Training sessions will be led by a certified RGM practitioner. Each 60 min group session will follow a structured format beginning with a 5 min warm-up period incorporating light stretching, relaxation techniques and breathing exercises. This will be followed by systematic progression through the symbol-based activities starting at a slow tempo of 50 beats per minute and gradually increasing in complexity and pace according to individual participant capabilities. Sessions will conclude with a 5 min relaxation period and opportunities for social interaction among participants.

The complete intervention protocol will involve twice-weekly group sessions conducted over 12 consecutive weeks under the guidance of the certified RGM practitioner who will adjust activity complexity based on participants’ physical capacities. To ensure transparency and reproducibility, comprehensive implementation details will be reported in the final publication following the Robb *et al*^42^ checklist for reporting music-based interventions as recommended by Consolidated Standards of Reporting Trials (CONSORT) guidelines. This will include detailed information on trainer qualifications and experience levels, group size, specific music selections with tempo progressions, music delivery method, intervention setting and treatment fidelity.

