### Waitlist control group

Participants randomised to the waitlist control group will continue with their usual daily activities during the 12-week intervention period. They will not receive any study-specific interventions during this time but will complete all outcome assessments according to the same schedule as the intervention group. Following completion of the 3-month follow-up assessments, waitlist control participants will be offered the opportunity to participate in the RGM training programme.

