### Randomisation procedure

Randomisation (1:1) will be conducted in four separate blocks corresponding to each study site: Gothenburg, Karlstad, Stockholm and Malmö. Microsoft Excel will be used for performing the randomisation based on participant identification numbers, with the process managed by an external researcher to ensure objectivity.

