### Sample size calculation

The sample size estimation was conducted using GPower software (V.3.1.9.7). The study’s primary outcome is the between-group difference in change of Mini-BESTest total scores postintervention. Based on Beauchamp *et al*,^62^ a minimal clinically important difference of 4 points was chosen, with a corresponding baseline SD of 6.5 points for the Mini-BESTest in a stroke outpatient cohort. This yields a standardised effect size of Cohen’s d=0.62 with an α error probability of 0.05 and desired power of 80% (1 – β=0.80). GPower indicates that 36 participants per group (72 total) are required to detect the specified effect size. To allow for up to 10% attrition, the total sample size was increased to 80 participants (40 per group).

Given that this is a multicentre trial conducted across four sites, we initially adjusted the sample size as per CONSORT recommendations for non-pharmacological treatments,^63^ to account for potential clustering effects due to differences between sites or instructors. The design effect was calculated by drawing on estimates from multicentre stroke rehabilitation literature, which typically report ICCs ranging from 0.007 to 0.031.^64^ An ICC of 0.01 was conservatively applied, as applying a higher ICC would have led to a larger sample size that was beyond the financial constraints of the current study and would have been unfeasible. Since the intervention will be delivered across four sites, we adjusted for potential clustering using a calculated design effect of 1.17 using the formula [1 + (*n*−1) × ICC], where *n* is the average cluster size and ICC is the intracluster correlation coefficient, which yielded a cluster-adjusted sample size requirement of 84 participants (approximately 21 per site).

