### Quantitative data analysis

All quantitative data will be analysed using both descriptive and inferential statistical methods. Prior to conducting hypothesis testing, data will be assessed for completeness, normality and the presence of outliers. The distribution of continuous variables will be evaluated using visual inspection and the Shapiro-Wilk test to determine the suitability of parametric or non-parametric analyses. Baseline characteristics between the intervention and control groups will be compared using Mann-Whitney U tests for continuous variables and χ^2^ tests for nominal variables to assess group equivalence. All analyses will follow the intention-to-treat principle, meaning that all participants will be analysed in the groups to which they were originally randomised, regardless of adherence or dropout. Any missing data will be managed using appropriate imputation strategies, depending on the pattern and mechanism of missingness. The effects of the intervention on primary and secondary outcomes will be examined using mixed-model repeated measures ANOVA (analysis of variance) or appropriate non-parametric alternatives, with time (baseline, postintervention, 3-month follow-up) and group (RGM vs control) as factors.

To address multiplicity in the analysis of the 13 secondary outcomes (FES-I, Memory Test, Victoria Stroop Test, Rey Complex Figure Test, SPPB, 10MWT, 6MWT, ODTA, 9HPT, SIS-16, MADRS, RAND-36 and EQ-5D-5L), the Benjamini-Hochberg False Discovery Rate (FDR) procedure will be applied to control the expected proportion of false positives. Effect sizes of the variables will be expressed using partial eta squared. All statistical analyses will be conducted using IBM SPSS Statistics (V.29.0.1), with the FDR procedure implemented using the SPSS syntax. A significance level of p<0.05 will be applied for the primary outcome, while FDR-adjusted p values will be used for secondary outcomes.

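### The model contains only time and group, although randomisation is by site and the sample size is inflated for clustering; the expected effect on the test is small but cheap to address

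*Protocol article*

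**What the plan says.** Four parts of the protocol article bear on this point.

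- **Randomisation procedure:** "Randomisation (1:1) will be conducted in four separate blocks corresponding to each study site". Site is therefore a stratification factor, and both arms are present at every site.
- **Intervention and Waitlist control group:** RGM is delivered as "twice-weekly group sessions conducted over 12 consecutive weeks under the guidance of the certified RGM practitioner". Of the controls, the article says: "They will not receive any study-specific interventions during this time". Clustering by training group or trainer can therefore arise in one arm only.
- **Sample size calculation:** the number was adjusted "to account for potential clustering effects due to differences between sites or instructors", using a design effect of 1.17, to give 84 participants. The ICCs cited range from 0.007 to 0.031; "An ICC of 0.01 was conservatively applied". The same section defines the primary outcome as the between-group difference in change in Mini-BESTest total score after the intervention.
- **Quantitative data analysis:** the method is a repeated-measures mixed ANOVA, or a non-parametric counterpart, and the section lists what enters the model: "with time (baseline, postintervention, 3-month follow-up) and group (RGM vs control) as factors". No section adds a term for site, trainer or training group, or a cluster-robust variance.

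**The concern.** The design section stratifies by site and the sample size section provides for clustering, but the model carries neither into the analysis. Recruiting more participants for clustering buys power. It does not correct a standard error computed as if all participants were independent.

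The two omissions work in opposite directions. Leaving out a stratification factor that is related to the outcome makes the standard error slightly too large. Leaving out a shared group or trainer effect in the RGM arm makes it slightly too small, so the p value is slightly too favourable to RGM. The primary test is judged at p<0.05 with a single model, so it is better to settle the model before the data are seen.

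**Working it through.** **The plan's own figure.** The design effect is 1 + (n − 1) × ICC. With n = 72/4 = 18 and ICC = 0.01 it is 1 + 17 × 0.01 = 1.17, and 72 × 1.17 = 84.24. This reproduces the stated 1.17 and 84, so the final sample size exists because of clustering.

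**Does that formula fit the design?** With whole-site n, it applies when entire sites are allocated to one arm. Here participants are randomised within sites, so an effect common to both arms of a site cancels from the treatment difference. The clustering that remains is within RGM training groups.

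**Which site effects matter for the primary test?** The primary comparison is of change, which is the group-by-time term in the stated model. A site difference that is constant over time drops out of each participant's change. Only site differences in change (site-by-time variation) remain.

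**Ignoring site-by-time variation.** Take the ICC as the site share of the variance of change. With randomisation within site, the model's SE divided by the correct SE is 1/√(1 − ICC).

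| ICC | SE ratio | Actual size of a 5% test |
|---|---|---|
| 0.007 | 1.004 | 4.9% |
| 0.01 | 1.005 | 4.9% |
| 0.031 | 1.016 | 4.6% |

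**Ignoring RGM-group clustering.** Assumptions: one RGM group per site, so m = 42/4 = 10.5; the cited ICCs apply to training groups; controls are independent.

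- RGM-arm design effect: DE = 1 + (10.5 − 1) × ICC
- Correct variance of the treatment difference relative to the model's: V = (1 + DE)/2
- Actual size of a nominal 5% test: 2 × [1 − Φ(1.96/√V)]

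| ICC | DE (RGM arm) | V | √V | Actual size |
|---|---|---|---|---|
| 0.007 | 1.067 | 1.033 | 1.016 | 5.4% |
| 0.01 | 1.095 | 1.047 | 1.023 | 5.5% |
| 0.031 | 1.294 | 1.147 | 1.071 | 6.7% |

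A simulation of the two-group comparison (40,000 replicates, four sites, 10 per arm per site) gave 5.5% at ICC 0.01 and 6.5% at 0.031.

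**Smaller groups.** With two groups per site, m = 5.25. At ICC 0.01, DE = 1 + 4.25 × 0.01 = 1.043 and V = 1.021, giving about 5.2%. At 0.031, DE = 1.132 and V = 1.066, giving about 5.8%.

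**Both effects together.** With site and group ICCs both at 0.031, the simulation gave 6.5% without a site term and 6.9% with a fixed site term. Adding site therefore does not deal with the group or trainer part.

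**The case against.** The strongest reply is that the effect is small and partly assumed. At the plan's own ICC of 0.01 the test runs at about 5.5% instead of 5%. The number of training groups and trainers per site is not given: the Intervention section leaves group size to the final report, and recruitment runs over two years, so several smaller groups per site are possible. The cited ICCs are described as coming from multicentre stroke rehabilitation studies, and using them for therapy groups is a further assumption. All of this stands and limits the weight of the point. If one trainer led several groups, however, trainer clustering would remain.

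A second reply is that a condensed article may leave model detail to an analysis plan. That is only a partial defence, because the article itself lists the factors, and the list does not match its own randomisation and sample size sections.

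Three stronger readings are tempting.

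- A reader might infer that leaving out site puts all between-site variance into the error of the primary test. It does not, because stable site differences cancel from change.
- A reader might infer that the test is badly inflated. An assumed group ICC of 0.10 would give about 10.7%, but the documents offer no basis for that value, which is more than three times the top of their cited range (0.10/0.031 = 3.2).
- A reader might infer that a site main effect alone cures the mismatch. It would leave the group-by-time test unchanged.

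**Conclusion.** The point holds in a limited form. The stated model does not match the stated design: site is a stratification factor and clustering is provided for in the sample size, but neither is in the analysis.

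Over the cited ICC range, with one RGM group of about 10.5 per site, the correct variance of the treatment difference is about 3 to 15% larger than the model's because of group or trainer clustering, and a nominal 5% test runs at about 5.4 to 6.7%. Ignoring site-by-time variation acts the other way and is smaller, with a size of about 4.6 to 4.9%. These figures rest on the assumed group structure and on applying site-level ICCs to training groups; more groups per site would reduce the inflation. The change should be made, but the omission does not by itself threaten the trial's conclusions.

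**What to change.** 1. In the primary and secondary models, include site and site-by-time as fixed terms. Alternatively, analyse week-12 Mini-BESTest adjusted for baseline, with site as a factor.
2. Prespecify a sensitivity analysis with a random training-group or trainer effect in the RGM arm only (a partially nested model), using small-sample degrees of freedom. Record each participant's training group and trainer so that it can be run.
3. State in the Sample size calculation section that the whole-site design effect of 1.17 is the cluster-randomised formula and does not describe randomisation within sites. Under the assumptions above, the matching value is V, about 1.03 to 1.15. This corrects the formula and is not a reason to recruit fewer: 84 is 72 × 1.17, so it does not contain the attrition allowance that raised 72 to 80.

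**Cost.** Items 1 and 2 are analysis wording plus one recorded variable. Site uses 4 − 1 = 3 degrees of freedom, and site-by-time uses 3 × 2 = 6 over three visits. With about four RGM groups the group variance is poorly estimated, resting on about 4 − 1 = 3 degrees of freedom. That is why the partially nested model is proposed as a sensitivity analysis and not as the primary analysis.

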### Qualitative data analysis

Qualitative data from focus group interviews will be transcribed verbatim from audio recordings into Swedish. The data will then be analysed using reflexive thematic analysis, as described by Braun and Clarke,^65^ with additional methodological guidance from Gale *et al*,^66^ supported by NVivo software to ensure systematic coding. The analysis will be conducted inductively, with themes derived directly from the data. The anonymised transcripts will be read repeatedly and independently by four researchers to identify meaning units and acquire a comprehensive understanding of the material. Meaning units, comprised of words or sentences corresponding to the research questions, will be compared until consensus is reached between researchers. These units will then be condensed into codes that remain close to the manifest content of the text, describing the material concisely while preserving its core meaning. The constant comparison method will be employed to synthesise data throughout the process. Subsequently, the codes will then be grouped into categories containing similar utterances under descriptive concepts. These categories will be merged into broader themes, each labelled with a description of their contents. Final themes will be agreed on by all members of the research team. Direct quotes from interviews will be included in the final synthesis to support findings and enhance credibility and trustworthiness.

## Ethics and dissemination

Ethical approval for this study has been obtained from the Swedish Ethical Review Authority (Etikprövningsmyndigheten, Dnr: 2025-01269-01). An amendment to expand the study from three to four centres was subsequently approved by the Swedish Ethical Review Authority (Dnr: 2025-08232-02). All participants will be fully insured during the course of the project, including travel to and from assessment and training locations, and during the training itself.

The current approved protocol version published on ClinicalTrial.gov registry (NCT06979050) is version 1 dated May 2025. Any modifications to the study protocol will be submitted as amendments to the Swedish Ethical Review Authority before implementation. Furthermore, during the course of the study, the participants will retain the right to withdraw from the study at any point without providing justification, and any data collected prior to withdrawal will be included in the final analysis according to the intention-to-treat principle.

Communication regarding the trial progress will be maintained through regular updates via professional networks of clinicians and RGM practitioners. On completion, trial findings will be submitted for publication in peer-reviewed rehabilitation and stroke journals, presented at national and international conferences focused on neurological rehabilitation and stroke recovery, and shared with relevant stakeholders and patient advocacy groups such as Strokeförbundet. The outcomes of this research will contribute to the evidence base for music-based interventions in stroke rehabilitation and inform the development of future clinical guidelines and research initiatives in this field.
